### Randomization

At the time of gastrectomy, if the patient has given informed, written consent and meets inclusion criteria, he will be peroperatively randomized, using an interactive Web response system. Randomization will be balanced and stratified by investigating center; because of the center’s influence in the most studies that evaluated HIPEC, and by the presence or absence of signet ring cells, based on the findings of the preoperative biopsies because of the recent demonstration of its particular prognosis and its relative chemoresistance.

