### Sample size calculation and statistical considerations

This study is designed as a randomized phase III in order to compare the 5-year overall survival in patients with advanced gastric carcinoma randomized to hyperthermic intraperitoneal chemotherapy administration versus that of patients randomized to control arm.

The hypotheses are the following: 5-year overall survival in the control group of about 30%
[9,10]; 5-year overall survival in the intervention group of about 45% (i.e. an HR of 0.67)
[45]; a maximum follow-up time of 5 years; an alpha of 5%, two-sided. With this hypothesis and to have a 80% power, a total of 306 patients will have to be randomized. Since 5% of patients are expected to excluded during surgery (peritoneal carcinomatosis), a total of 322 patients will be included.

The effectiveness analysis will be carried out on the intention-to-treat population, defined as all patients included. A second analysis will be conducted on the “treated” population, determined according to the treatment actually administered (*per protocol* analysis). Overall survival will be measured from the date of surgery up to the date of death, regardless of the cause, or to the end of follow-up (5 years). The Kaplan-Meier method will be used to estimate the survival curves. Median survival will also be given and differences between the two groups assessed using a logrank test. This analysis will then be confirmed using a Cox regression analysis taking into account the center effect (frailty Cox model). The conditions for using the Cox regression analysis will be checked.

An intermediate analysis of toxicity will be realized at least every six months or every 50 patients randomized from the start of patients’ recruitment. The number of SAEs and AEs of severe (grade III-IV) with their accountability will be described.

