[51]. Recently, excellent results in treating colorectal peritoneal carcinomatosis have been reported for the use of HIPEC with oxaliplatin, with an exposure time of just 30 minutes. Furthermore, a French randomized, phase III study is currently assessing the use of HIPEC with oxaliplatin associated with complete cytoreductive surgery (CCS) to treat colorectal peritoneal carcinomatosis. These three studies used a dose of 460 mg/m^2^ of oxaliplatin for the open-abdomen technique and 350 mg/m^2^ for the closed-abdomen technique, administered in 2 liters/m^2^ of 5% glucose with the systemic administration of induction chemotherapy using FU/Leucovorin (400 mg/m^2^ 5-FU and 20 mg/m^2^ of folic acid) to increase the cytotoxic effect of the oxaliplatin. Glehen et al. recently published a report on the French experience in the curative treatment of gastric peritoneal carcinomatosis
[30]. The mortality rate was high, and reached 6%. This may be explained by the fact that the gastrectomy-HIPEC association increases the risk of severe postoperative complications. It would seem preferable to arbitrarily reduce the dose of oxaliplatin (250 mg/m^2^) in order to avoid an excessive rate of postoperative complications resulting from the experimental treatment.

The incidence of signet ring cell adenocarcinoma is steadily increasing in Western countries
[52,53]. Recent data has suggested not only that is has a negative prognostic value
[22], but that it is also chemo-resistant

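### Randomisation is stratified by signet-ring status for its prognosis, but the stated logrank test and Cox model leave that factor out, at a small cost in efficiency

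*Protocol article*

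**What the plan says.** Protocol article, Randomization: "Randomization will be balanced and stratified by investigating center", and also "by the presence or absence of signet ring cells, based on the findings of the preoperative biopsies". The reason given for the second factor is "because of the recent demonstration of its particular prognosis and its relative chemoresistance". The Discussion repeats that signet-ring histology has been reported to be adverse ("not only that is has a negative prognostic value"), and the Background lists it among the factors favouring peritoneal recurrence.

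Protocol article, Sample size calculation and statistical considerations: Kaplan-Meier curves are planned, with "differences between the two groups assessed using a logrank test". No strata are named. The next sentence reads "This analysis will then be confirmed using a Cox regression analysis taking into account the center effect (frailty Cox model". Centre is the only factor that the model is said to take into account.

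The same section fixes the planning values: 5-year overall survival of 30% against 45%, a hazard ratio (HR) of 0.67, two-sided alpha of 5%, 80% power and 306 randomised patients.

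**The concern.** The design and the stated analysis do not match. Two factors define the randomisation strata. The analysis text names one of them, centre, for the Cox model, and omits the one chosen for its prognosis.

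Balancing allocation within signet-ring strata removes part of the chance variation between the arms. The plain logrank variance gives no credit for that, so it is too large for the design and the test rejects less often than its nominal level. In addition, when a prognostic factor is left out, the HR over the whole population lies nearer to 1 than the HR within strata. Both effects cost power.

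What is at stake is efficiency, not validity. The trial is sized at 80% power, and the factor has to be recorded before each patient is randomised, so using it needs no new data.

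**Working it through.** **1. The plan's own figure.** HR from the survival rates: ln 0.45 / ln 0.30 = 0.663. Freedman events: (1.96 + 0.8416)² × [(1 + 0.663)/(1 − 0.663)]² ≈ 7.849 × 24.39 ≈ 191.4. Mean 5-year death probability: (0.70 + 0.55)/2 = 0.625. N = 191.4/0.625 ≈ 306. The stated 306 reproduces.

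**2. Inputs that the document does not give.** Signet-ring prevalence and its mortality HR are assumptions, so ranges are shown. Common settings: 306 patients, exponential survival, control 5-year survival calibrated to 30%, censoring at 5 years, allocation balanced within signet-ring strata, no centre effect.

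**3. Treatment HR of 0.663 within each stratum.** Prevalence 30% and 50%, 20 centres assumed, blocks of 4 within centre by signet-ring strata, 6,000 runs per cell. Ranges span the two prevalences.

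| Signet-ring HR | True alpha, plain | Power, plain | Gain from stratifying (points) |
|---|---|---|---|
| 1.3 | 4.7–5.3% | 80.3–80.8% | 0.2–0.3 |
| 1.5 | 4.5–4.7% | 79.8–80.1% | 0.6–1.4 |
| 2.0 | 4.0–4.4% | 78.3–78.6% | 2.9–3.2 |
| 3.0 | 3.2–3.7% | 73.1–73.3% | about 8 |

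The stratified logrank keeps 80 to 82% power and a true alpha of 4.7 to 5.6% throughout. With no signet-ring effect the two tests do not differ. Monte Carlo standard error is about 0.3 points for alpha and 0.5 for power.

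**4. Is that the planned effect?** Not quite. Take 40% prevalence and a signet-ring HR of 2.0, and let u be 5-year survival in control patients without signet-ring cells.

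- Control arm at 30%: 0.6u + 0.4u² = 0.30, so u = 0.3956.
- Experimental arm with a within-stratum HR of 0.663: 0.3956^0.663 = 0.5407, so overall survival is 0.6 × 0.5407 + 0.4 × 0.5407² = 44.1%, not 45%.
- To reach 45%: 0.6v + 0.4v² = 0.45, so v = 0.5490. The within-stratum HR must then be ln 0.5490 / ln 0.3956 = 0.647.

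At signet-ring HRs of 1.5 and 2.5, the setting in step 3 gives 44.7% and 43.5%. Part of the low power in step 3 therefore comes from simulating a smaller overall benefit than the plan assumes.

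**5. Both calibrations at 40% prevalence.**

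| Signet-ring HR | HR 0.663 within strata: plain / stratified | Arms fixed at 30% and 45%: plain / stratified |
|---|---|---|
| 1.5 | 80.6 / 81.8% (+1.2) | 81.8 / 82.8% (+1.0) |
| 2.0 | 78.8 / 82.0% (+3.2) | 82.7 / 84.9% (+2.2) |
| 2.5 | 75.5 / 80.9% (+5.4) | 84.2 / 88.8% (+4.6) |

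A repeat of the first calibration at HR 2.5 gave 74.8 against 81.3% (+6.5), which sets the upper end of the 5 to 7 point range. The plain test's true alpha at HR 1.5, 2.0 and 2.5 was about 4.7, 4.3 and 3.2%. A repeat gave 4.7, 4.0 and 3.6%.

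**6. In patients.** At a signet-ring HR of 2.0 under the first calibration, the normal approximation gives (1.96 + 0.7995)² / (1.96 + 0.9154)² = 0.921. That is about 8% of the information, or some 24 of 306 patients. Under the second calibration, (1.96 + 0.9424)² / (1.96 + 1.0322)² = 0.941, or about 18 patients.

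**The case against.** **The article may only be brief.** It never calls the logrank unstratified, and strata and covariates often go into an analysis plan that is not shown. This limits the point, since that plan may already stratify. It does not remove it: the article does say which design factor the Cox model uses, and names only one of the two.

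**The size is assumed.** This stands. The document gives neither prevalence nor HR. It describes the prognosis as particular and negative. A reader might take signet-ring status to be strongly prognostic, but the text does not say so, and at an HR of 1.3 or below stratifying gains next to nothing.

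**The trial is not left short of power.** A reader might infer from step 3 of the working that the plain test misses its 80%. The plan, however, is written in overall survival, 30% against 45%. With both arms set to those values the plain test has about 82 to 84% power, and stratifying adds to that.

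**Nothing is biased.** This also stands. The error is on the safe side. The HR nearer to 1 is a marginal estimate of a different quantity, and the planned 0.67 itself comes from overall survival rates.

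**Other factors.** One might go on to adjust for preoperative chemotherapy, cytology or nodal status. None is a stratification factor, and any gain would rest on further assumptions, so the mismatch gives no ground for adding them. The plain logrank as described also ignores centre. The calculations assume no centre effect and do not bear on that.

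**Conclusion.** The point holds as a modest efficiency issue. The stated analysis omits a randomisation factor chosen for its prognosis, which makes the logrank mildly conservative and less efficient than the design allows. With 40% signet-ring prevalence assumed, the gain forgone is about 1 power point at a signet-ring HR of 1.5, about 3 at 2.0 and 5 to 7 at 2.5, with the plain test's true alpha roughly 4.7, 4.3 and 3.2%. The direction is firm for any prognostic stratification factor. The size is not, because it depends on two figures that the document does not give.

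The documents do not support reading this as inflated type I error, a biased estimate or a failure to reach the planned 80% power.

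**What to change.** Before the analysis, state that the primary logrank is stratified by signet-ring status as recorded at randomisation. Add signet-ring status to the centre-frailty Cox model, as a stratum or a covariate, and keep the unstratified logrank as a sensitivity analysis. If an unpublished analysis plan already does this, it is enough to confirm it.

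The cost is a sentence or two of wording, with no new data and no more patients. The one small downside is that the reported HR becomes conditional on signet-ring status instead of marginal, which the report should say.

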### Ancillary study

A cytological ancillary study will be performed. The aim of this exploratory study is to compare the incidence of positive peritoneal cytology pre- and post-gastrectomy in the two arms of the study (Am A and Arm B), and to assess its impact on 5-year survival. A standardized procedure for peroperative peritoneal cytological sampling was previously approved under a large, French, multi-center prospective study (EVOCAPE 2, PHRC 2001 Funding) and will be followed for the pre- and post-gastrectomy sampling
[46]. Samples will be separated into 2 aliquots. After sedimentation overnight at room temperature, the material will be centrifuged at 1500 RPM for 5–10 minutes. The cell pellet will be aspirated, smeared on Superfrost PLUS glass slide and dessicated (2 slides) or fixed with methanol (one additional). Smears will be stained with MGG in an Hematek 2000 (Bayer^©^) automaton, and with Papanicolaou. For every case, the remaining cell pellet will be submitted to the cell block technique (Shandon Cytoblock Kit®) for Haematoxylin and eosin control and immunohistochemistry. Immunohistochemistry performed on cell blocks using at least CEA (monoclonal and polyclonal) and cytokeratin 20, the Cytokine-like High Mobility Group Box 1 (HMGB1)
[47] will also be considered. Positive samples will be defined by the presence of either tridimensional clusters of malignant cells, or by the presence of unequivocal isolated malignant cells. The presence of cell and nuclear atypias (cell balls not mesothelial in origin, epithelial cells with increased N/C ratio, enlarged nuclei, irregular nuclear borders, and prominent nucleoli) will be considered necessary for the positive morphological diagnosis, as previously reported
[46]. Additionally, cases with CEA- and/or CK20-reactive epithelial cells will be considered positive, whatever their morphological aspect. Negative samples will be defined by the absence of malignant cells after conventional stains and immunohistochemistry (no CEA and/or CK20 immunoreactivity). Peritoneal samples taken before and after surgery will be fixed with 1/3 carbowax (20% polyethylene-glycol 1500 in 50% ethanol) and sent as rapidly as possible to the laboratory in 100 to 500 mL vials, according to the amount of fluid. Cells will be allowed to sediment overnight at room temperature. The lower part of the fluid will then be aspirated and treated as previously described (see the lab. technique) for smearing, cell blocks and immunohistochemistry.

The number of pre- and post-gastrectomy positive cytologies will be calculated. The percentage of pre- and post-gastrectomy positive cytologies will be compared using Mcnemar’s test. A Cox regression model will be used to assess the impact of peritoneal cytology on 5-year overall survival. The conditions for using Mcnemar’s test and the Cox regression analysis will be checked.

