### Surgical technique

At the opening of the abdomen, surgical exploration will be performed in order to compare data collected at preoperative videolaparoscopy with current operative findings including the effects coming from preoperative chemotherapy, namely the downstaging as far as T parameter is concerned, presence of serosal involvement and its extent, the absence of distant metastases and the feasibility of a D1-D2 resection with curative intent.

Peritoneal washing will then be performed: the abdomen will be irrigated with 200 ml of 0.9% NaCl solution (normal saline), left in the peritoneal cavity for 2 minutes and then all fluid will be aspirated from the four abdominopelvic quadrants [Left Upper Quadrant (LUQ) - Right Upper Quadrant (RUQ) - Left Lower Quadrant (LLQ) - Right Lower Quadrant (RLQ)]. All the collected fluid will be sent to the corresponding lab, where specimens for regular cytological analysis, cell blocks and immunohistochemistry (ancillary cytological study) will be sent to the Centre de Biologie et de Pathologie Est – Hospices Civils de Lyon.

All the patients will undergo a D1-D2 gastrectomy, carried out according to Japanese guidelines and to the European recommendations for the preservation of spleen and pancreas
[42]: lymphadenectomy will consist of removal of nodal groups 2 to 9 as specified by the JGCRS; group 1 will be added when total gastrectomy is performed and group 12 in distal cancers. *Ex vivo* separation of lymph node groups in individual containers before the surgical specimen is submitted to the pathologist is recommended. At the end of the gastrectomy procedure the peritoneal washing will be repeated with the same procedure.

Following randomization, the patients treated into the experimental Arm receive intravenous 5-FU 400 mg/m^2^ + calcium levofolinate 10 mg/m^2^) as systemic chemotherapy induction for HIPEC 15 min before HIPEC started. At the end of the procedure the patients in the experimental Arm will undergo HIPEC.

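### In the exploratory cytology study, any CEA- or CK20-reactive epithelial cell counts as positive without atypia, which leaves the pre/post-gastrectomy comparison open to an upward bias of unknown size

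*Protocol article*

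**What the plan says.** All of this is in the protocol article, mostly under Ancillary study.

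- **Status.** "The aim of this exploratory study is to compare the incidence of positive peritoneal cytology pre- and post-gastrectomy" in the two arms, and to assess its impact on 5-year survival.
- **Morphological route to a positive result.** Malignant clusters or unequivocal single malignant cells are needed, and cell and nuclear atypia "will be considered necessary for the positive morphological diagnosis".
- **Immunohistochemical route.** "Additionally, cases with CEA- and/or CK20-reactive epithelial cells will be considered positive, whatever their morphological aspect".
- **Negative result.** "Negative samples will be defined by the absence of malignant cells after conventional stains and immunohistochemistry (no CEA and/or CK20 immunoreactivity").
- **Samples covered.** "Peritoneal samples taken before and after surgery will be fixed with 1/3 carbowax", after which both go through the same smear, cell-block and immunohistochemistry steps.
- **Timing (Surgical technique).** The first washing is done on opening the abdomen. Then: "At the end of the gastrectomy procedure the peritoneal washing will be repeated with the same procedure". HIPEC is described after this step.
- **Analysis.** "The percentage of pre- and post-gastrectomy positive cytologies will be compared using" McNemar's test, and "A Cox regression model will be used to assess the impact of peritoneal cytology on 5-year overall survival".

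**The concern.** The two routes to a positive result do not carry the same safeguard. The morphological route demands atypia. The immunohistochemical route drops it, and the definition of a negative sample closes the remaining exit: a reactive but bland epithelial cell can be neither negative nor indeterminate, so it must be positive.

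This matters because the gastrectomy is the event between the two samples. In an undisturbed abdomen, reactive epithelium in the washing is reasonable evidence of tumour. Once the stomach has been cut, benign lining cells have a possible way into the cavity. If some of them stain, the same rule is less specific in the second washing than in the first.

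McNemar's test uses only the discordant pairs, and such errors would be mainly pre-negative/post-positive pairs. They would look exactly like malignant cells shed by the operation. In the Cox model for post-gastrectomy cytology, false positives would sit among the true ones and tend to dilute any prognostic effect. The Discussion says that a postoperative increase has so far been suggested only by small studies and that its prognostic value is unsettled. The misclassification bears on both questions.

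**Working it through.** **Inputs from the protocol article.** 306 patients randomised, taken here as 306 complete pairs. Two-sided 5% significance, stated for overall survival and assumed for McNemar's test. Control and intervention 5-year survival of 30% and 45%, and 80% power.

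**Inputs that are assumptions.** The documents give none of these:
- p, the share positive before gastrectomy (20%; range 10% to 30%)
- d, genuine discordance in each direction (2%; also 0 and 3%)
- f, the share of otherwise negative second washings made positive only by benign reactive epithelium (0 to 10%)

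**Step 1: the plan's own figure.** The ancillary study has no sample size of its own. The 306 reproduces:
- HR = ln 0.45 / ln 0.30 = 0.663
- Freedman events = (1.96 + 0.84)² × (1.663/0.337)² ≈ 191.4 (unrounded inputs)
- Mean event probability = (0.70 + 0.55)/2 = 0.625
- 191.4/0.625 = 306.3

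The cytology rule does not enter this calculation.

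**Step 2: smallest false result.** With no other discordance, m post-only pairs against none give an exact two-sided p of 2 × 0.5^m. For m = 5 this is 0.0625; for m = 6 it is 0.031. Six of 306 pairs is 2%.

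**Step 3: allowing for genuine discordance.** With no true net change:
- P(pre-negative, post-positive): b = d + (1 − p − d) × f
- P(pre-positive, post-negative): c = d × (1 − f)
- Excess in the second washing: b − c = (1 − p) × f

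Example, p = 20%, d = 2%, f = 5%: b = 0.02 + 0.78 × 0.05 = 0.059 and c = 0.02 × 0.95 = 0.019. The excess is 4.0 points, with about 18.1 against 5.8 expected discordant pairs in 306. The chance of a significant rise is the exact McNemar rejection probability summed over the distribution of the discordant pairs.

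| f | b | c | Excess (points) | Chance of a falsely significant rise |
|---|---|---|---|---|
| 0 | 2.00% | 2.00% | 0 | 1% |
| 0.5% | 2.39% | 1.99% | 0.4 | 3% |
| 1% | 2.78% | 1.98% | 0.8 | 6% |
| 2% | 3.56% | 1.96% | 1.6 | 16% |
| 3% | 4.34% | 1.94% | 2.4 | 31% |
| 5% | 5.90% | 1.90% | 4.0 | 66% |
| 10% | 9.80% | 1.80% | 8.0 | 99% |

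**Step 4: sensitivity to the assumptions.**
- p = 20%, d = 0: f of 1%, 2% and 5% gives 4%, 37% and 98%.
- p = 20%, d = 3%: f of 1%, 2%, 5% and 10% gives 5%, 12%, 55% and 97%.
- d = 3%, f = 5%: p of 10%, 20% and 30% gives 64%, 55% and 45%.

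**Step 5: the Cox model.** With d = 0, the share of post-positive samples that are false is (1 − p)f / [p + (1 − p)f]. At f = 5% this is 31%, 17% and 10% for p of 10%, 20% and 30%. The direction is dilution. Its size in hazard-ratio terms cannot be derived without survival figures by cytology status, which the documents do not give.

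**The case against.** **The mechanism rests on facts outside the documents.** Nothing in the protocol article says that normal digestive epithelium reacts for CEA or CK20, that it reaches the washing, or how often. This stands. A reader might infer that benign cells will be scored as cancer and that the comparison is biased. The documents support only a risk of unknown size, and at 1% contamination or less it is small.

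**The error is not strictly one-sided.** A reader might also infer that only the second washing is exposed. The rule covers both samples, and the inclusion criteria admit perforated tumours, in which the lumen may already communicate with the peritoneum before the first washing. This stands too: the error would fall mainly, not only, on the second sample.

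**The scope is narrow.** The study is labelled exploratory. Overall survival, the logrank test and the 306 are untouched. The second washing is described before HIPEC, so contamination should be similar in the two arms and should not bias a contrast between them. All of this is accepted.

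**Sensitivity against specificity is a legitimate choice, and secondary analyses are often left to the SAP.** This stands in part. It is a good argument against insisting on a new definition of a positive sample. It does not answer the point itself, because the article fixes the rule explicitly, and the rule as stated merges the two kinds of positive. An earlier multicentre study is cited for the sampling procedure and the morphological criteria; it is not available here and cannot be credited with a safeguard.

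**Conclusion.** The concern holds as a risk of misclassification in an exploratory analysis. As written, reactivity alone makes a sample positive, overriding the atypia requirement. Because the resection lies between the washings, benign reactive epithelium released by surgery would push the pre/post comparison upwards and tend to weaken the association of post-gastrectomy cytology with survival. Nothing in the text separates this from malignant shedding.

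The size cannot be fixed from the documents. In the base case it runs from negligible (3% false rises at 0.5% contamination, 6% at 1%) to decisive (66% at 5%, 99% at 10%). These figures rest on 306 complete pairs, no true change and the assumed positivity and discordance. The documents do not support a claim that the trial's efficacy conclusion or its between-arm comparisons are at risk. The point is worth acting on because the remedy is so cheap.

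**What to change.** At both washings, record two categories separately: samples positive by the morphological criteria already given under Ancillary study, and samples positive by immunohistochemistry alone without atypia. The existing overall definition can stay.

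Repeat McNemar's test and the Cox model with morphology-positive cases only, and report both sets of results. State in advance that a rise resting on immunohistochemistry-only cases will not be read as evidence that gastrectomy sheds malignant cells.

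Cost: one extra field in the cytology record and a little more analysis, on the same samples, slides and stains. The morphology-only analysis will be less sensitive for scant, bland-looking tumour cells; showing it beside the overall result makes that loss visible.
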